### Randomisation

After written informed consent has been received, an independent investigator using a stratified block randomisation scheme will assign participants to CAU or BPR. Stratification factors are ‘centre’ and ‘employment in the preceding year (yes/no)’. The group with eating disorders has an additional stratification factor: ‘duration of hospitalisation in the 6 months prior to inclusion (less/more than 3 months)’ because this group in particular needs support with rehabilitation goals directly after hospitalisation. In order to avoid large differences between both conditions in the level of costs during the period before commencement of the study, duration of hospitalisation will be added as an extra stratification factor for this group. Random allocation to either experimental group or control group will take place immediately after the baseline measurements have been completed.

### Blinding

Patients, MH professionals and research staff cannot be blinded to the allocated intervention after randomisation. However, interviewers who gather data will remain blind to treatment condition. Furthermore, research assistants blinded to treatment allocation will enter data, and research staff will only perform statistical analyses on final, anonymous datasets.

### Statistical analyses

#### Primary clinical analyses

The primary analyses will be performed according to the ‘intention to treat’ principle: all patients, including those who did not initiate or complete a rehabilitation process, will remain in the group as assigned. Missing items will be handled according to questionnaire instructions and standards. Furthermore, data will be collected from multiple sources (patients and workers), which allows indirect judgements to be used as proxies of missing data if needed.

To analyse results on the main outcome, the difference in percentage of patients with increased participation in both groups after 1 year will be compared. Firstly, descriptive statistics will be performed with regard to the proportions of patients with increased participation. Secondly, risk differences yielding numbers needed to treat (NNT) will be calculated using (multilevel) regression models to be adjusted for research centre and employment in the year preceding the study. Other possible confounders such as sociodemographics, psychiatric symptoms and remission, quality of the therapeutic relationship or educational level of MH professional will be added if comparison between intervention group and control group shows differences between these groups despite randomisation. In addition, sensitivity analyses will be performed on all outcomes, including only respondents who participated in at least two contacts with the rehabilitation worker and excluding patients for whom the outcome was rated indirectly because they were not available for interviews at 6 and 12 months. Secondary outcomes are (I) continuous variables indexing quality of life, psychosocial functioning, recovery and self-efficacy and (II) binary variables indexing patients’ experience of success in achieving their rehabilitation goals (yes/no). Patients’ experience of success in achieving their rehabilitation goals could also be presented as an (III) ordinal variable (yes/no/partially). Means and proportions of these variables at baseline, 6 and 12 months will be modelled using both multilevel linear and logistic regression analyses in which each person (level 2) contributes three observations (level 1), making adjustments for participating centre, and other confounders. Treatment effects will be quantified using the Time (baseline, 6 and 12 months) × Group (BPR and CAU) interaction, assessing whether change in the outcome of interest over time differs significantly between the two groups. Effects of time stratified by treatment group will be calculated by linear combination of the appropriate terms in the model using the General Linear Model (GLM) procedure in SPSS.

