### Other measures

The following measures include data on possible confounding and/or mediating variables.*Sociodemographic information* will be gathered by means of a structured interview scheme at the start of the study and checks will be performed in the interviews that follow at 6 and 12 months.*Psychiatric symptoms and remission* are measured with the Brief Psychiatric Rating Scale [65–67] in order to control for large changes in symptomatic functioning. The BPRS was developed as a quick and efficient method to describe and evaluate change in psychiatric symptoms. We use the 24-item version which measures the following symptoms: 1) Somatic concern, 2) Anxiety, 3) Depression, 4) Suicidality, 5) Guilt, 6) Hostility, 7) Elevated Mood, 8) Grandiosity, 9) Suspiciousness, 10) Hallucinations, 11) Unusual thought content, 12) Bizarre behaviour, 13) Self-neglect, 14) Disorientation, 15) Conceptual disorganisation, 16) Blunted affect, 17) Emotional withdrawal, 18) Motor retardation, 19) Tension, 20) Uncooperativeness, 21) Excitement, 22) Distractibility, 23) Motor hyperactivity, 24) Mannerisms and posturing. Items are answered on a 7-point Likert Scale. Every scoring option has a short description of behaviours that must be observed for that particular score. The psychometric properties of the BPRS have often been investigated and BPRS has proven to be a reliable and valid instrument [68, 69]. Internal consistency is good with alphas >0.70.*Overall level of psychological, social and occupational functioning* is measured with the Global Assessment of Functioning (GAF), symptoms and disabilities version (GAF-SD) [70]. GAF is scored on a scale ranging from 0 to 100 with higher scores reflecting fewer symptoms (GAF-S) and handicaps (GAF-D). The GAF-SD has proven to be a reliable and valid measure of psychiatric disturbance in a sample of people with SMI.*Quality of the therapeutic relationship* is measured with the Helping Alliance Scale (HAS) [71]. The HAS was originally developed to measure the quality of the therapeutic relationship from the client’s point of view but an adapted version for the professional’s point of view also exists. Both versions consist of five items concerning the therapeutic relationship. Items are scored on an 11-point visual analogue scale ranging from 0 = not at all to 10 = entirely, with marked 10 mm intervals. Additionally, the client version has a sixth item asking about how patients feel immediately after seeing their MH professional which is answered with unchanged, better or worse. The professional version has two additional open items that ask about positive and negative aspects of the therapeutic relationship. So far, the HAS has not been psychometrically evaluated but has been used in several studies investigating the therapeutic relationship [71–73].*Uptake of the intervention* will be assessed by gathering detailed information about drop-out and non-adherence during the trial.

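### The primary model adds further covariates when the arms are seen to differ and does not confine them to pre-randomisation values, so it can adjust for consequences of allocation

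*Protocol article*

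**What the plan says.** Under Primary clinical analyses, the risk difference and NNT come from (multilevel) regression models "to be adjusted for research centre and employment in the year preceding the study". Those two covariates are unconditional, and they are stratification factors for the main group. A second set is conditional. It starts with sociodemographics and with symptoms and remission, and continues: "quality of the therapeutic relationship or educational level of MH professional will be added if comparison between intervention group and control group shows differences". The condition is a comparison of the arms that "shows differences between these groups despite randomisation". The same section declares the primary analyses to be by intention to treat.

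Under Other measures, the list that contains the symptom scale (BPRS) and the alliance scale opens with: "The following measures include data on possible confounding and/or mediating variables". Symptoms are measured "in order to control for large changes in symptomatic functioning". The therapeutic relationship "is measured with the Helping Alliance Scale (HAS"), with no time point given.

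Under Randomisation, allocation "will take place immediately after the baseline measurements have been completed". Under Interventions, BPR is delivered by workers fully trained in the method, and CAU by other workers who have had no specific BPR training.

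**The concern.** A covariate measured before randomisation can differ between arms only by chance, and adjusting for it leaves the estimated effect of assignment intact. A covariate that arises after allocation can differ because of the treatment. Adjusting for it removes whatever part of the effect passes through it. It can also introduce bias from factors that influence both that covariate and the outcome.

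The rule does not separate the two kinds, and its trigger works in the wrong direction for the second. If BPR produces a better working relationship, the arms differ, the relationship enters the model, and that part of the benefit is subtracted from the headline risk difference and NNT. Separately, if the model is chosen after looking at arm differences, the nominal 5% error rate and the confidence interval do not allow for that choice.

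**Working it through.** **1. Where each conditional covariate falls relative to randomisation**

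- *Sociodemographics.* Collected at the start of the study, so pre-randomisation. Adjustment is harmless; only the data-driven selection is a problem.
- *Psychiatric symptoms and remission.* A baseline BPRS is pre-randomisation. The stated purpose, however, is to control for changes, and a change is post-baseline. The Background section also associates employment with fewer symptoms, so symptom change may partly follow from the outcome itself.
- *Therapeutic relationship.* No time point is stated. A score about the worker supplied by the assigned arm is post-allocation.
- *Worker's educational level.* Not a patient baseline characteristic. It depends on which worker the arm supplies. The stated minimum is four BPR and three CAU workers per centre, so over three centres 3 × 4 = 12 against 3 × 3 = 9. With so few workers, staffing alone could produce an arm difference.

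For the last three, an observed difference can be a consequence of allocation.

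**2. The planned effect**

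Sample size section: 11.5% against 0%, so the difference is 11.5 points and the NNT is 1/0.115 = 8.7. With n per arm, the usual two-proportion power is Φ{[Δ√n − 1.96√(2p̄(1−p̄))] / √(p1(1−p1)+p2(1−p2))}. For n = 90 this is Φ{[0.115 × 9.487 − 1.96 × 0.329] / 0.319} = Φ(1.40) = 92%. The protocol states 80% at 90 per arm. Its inputs need only 64 per arm, or 80 with continuity correction, so 90 is on the cautious side and is not in dispute here.

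**3. How often the trigger fires on a real treatment effect (illustration)**

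Assume a 5% test for an arm difference, 90 per arm, and a shift of a SD in alliance caused by BPR. The test statistic is centred on a√(n/2) = 6.71a. The protocol gives none of these inputs except n.

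| a (SD) | centre | alliance selected |
|---|---|---|
| 0.3 | 2.01 | about 50% |
| 0.5 | 3.35 | about 91% |
| 0.8 | 5.37 | about 100% |

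**4. What adjustment then removes (illustration)**

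In a linear model, total effect = direct effect + a × b, where b is the covariate's effect on success. The adjusted model estimates the direct part. Let s be the assumed share of the 11.5 points that runs through the covariate.

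| s | adjusted difference, 11.5 × (1 − s) | NNT | power at 90 per arm against 0% |
|---|---|---|---|
| 0 | 11.5 | 8.7 | 92% |
| 10% | 10.4 | 9.7 | 89% |
| 25% | 8.6 | 11.6 | 82% |
| 50% | 5.8 | 17.4 | 64% |

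The document gives no value for s. If BPR worsened the covariate, or if unmeasured factors drove both covariate and outcome, the bias could run the other way.

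**5. How often the trigger fires on nothing**

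For k independent covariates with no true difference, each tested at 5%, the chance that at least one differs is 1 − 0.95^k. That is 19% for k = 4 and 34% for k = 8. The adjustment set would therefore vary from one replication of the trial to another even without any true imbalance.

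**The case against.** The strongest reply is that the rule describes an ordinary baseline balance check. The wording about differences arising in spite of randomisation suits that reading, and all participants are already in care with the participating organisations. BPR and CAU workers share a team environment, so a patient may know the worker beforehand and an alliance score could be taken at baseline. This stands as far as timing goes: a reader might infer that patients meet their worker only after randomisation, and the document does not say so. It does not rescue the rule, which is not limited to baseline values and sits beside a stated aim of controlling for symptom change.

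Second, educational level is not BPR training, the professions in the two arms largely overlap, and nothing says that workers are randomised. A staffing difference could confound a comparison of techniques, which the contamination section names as the focus. That supports a labelled secondary analysis, not the intention-to-treat estimate. A reader might also infer that the protocol itself calls worker education a possible mediator; it does not, because Other measures does not list it.

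Third, crude proportions are to be described before modelling, so an unadjusted difference would be visible. That is a partial safeguard, but the NNT is to come from the model.

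Fourth, thresholds and time points are commonly left to the SAP. Their absence is not the complaint. The complaint is the rule that the article does state.

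**Conclusion.** The rule is wrong as written and should be corrected before analysis. It selects covariates for the primary model on observed arm differences, and the eligible list admits variables that allocation can influence. Adjusting for them can bias the intention-to-treat risk difference and the NNT, towards the null if BPR improves a variable that promotes participation.

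Three stronger readings are not supported. Not every covariate is conditional: centre and prior-year employment always enter. Adjustment does not always shrink the effect, because the direction depends on how BPR moves the covariate and on what else drives it. No particular percentage loss can be claimed, because the mediated share is unknown; the figures in the working rest on assumed shares and an assumed 5% selection test. What does not depend on those assumptions is that the model is data-dependent and that post-allocation covariates are not excluded from it.

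**What to change.** Delete the provision that adds covariates when the arms differ. State the primary model in advance: centre, prior-year employment and, if wanted, named covariates measured before randomisation, such as baseline BPRS, kept in whatever the observed balance. Move post-baseline alliance, symptom change and worker education to analyses labelled as mediation or sensitivity analyses, reported apart from the primary risk difference and NNT. If an alliance score is taken before randomisation and is wanted as a covariate, name it as such with its time point.

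The cost is a change of wording in the analysis section or the SAP. It needs no new data, no extra patients and no change to trial conduct.

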### Interventions

#### Experimental group: Boston Psychiatric Rehabilitation (BPR)

Patients in the experimental group will take part in rehabilitation sessions based on BPR, which uses a methodology that helps patients achieve and retain their rehabilitation goals [24, 37, 38]. The approach consists of four phases:Exploring: the client is supported in discovering what he/she wants to achieve.Choosing: the client is supported in choosing a goal in a rehabilitation area such as work or housing.Getting: the client is supported in carrying out the necessary interventions to attain the goal.Keeping: the client is supported in keeping the attained goal.

Patients do not need to have a clearly defined idea or plan for change in order to receive BPR because an important component of BPR is helping patients explore their options. Therefore, BPR attends to the needs of patients who have been suffering from mental illness for a long time and have lost confidence in their own ability to initiate change. Participants assigned to BPR will be offered at least one session every 2 weeks with an experienced BPR rehabilitation worker. There is no predefined maximum or minimum number of sessions that must be completed. Instead, patient and BPR worker plan sessions by agreement. However, BPR workers are obliged to offer one session every 2 weeks. The total number of sessions and duration of the period in which patient and worker cooperate will be registered. The intervention will be carried out by rehabilitation workers fully trained in the methodology (social workers, MH nurses, occupational and vocational therapists) who have practised with at least four patients under the supervision of a certified expert in BPR. Each participating centre will take part by involving at least four workers experienced in BPR in the BPR condition. Each worker will have an additional caseload of four research patients a year. In all three centres, a sufficient number of professionals with BPR training are available to carry out the intervention.

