Although MH professionals working according to FACT or RIRC guidelines (social workers, MH nurses, occupational therapists or employment specialists) may be familiar with rehabilitation, they have not received specific training in BPR. They offer additional support to patients in clarifying and achieving their rehabilitation goals on the basis of generic MHC models: mental health nursing care, social work and vocational rehabilitation programmes. All CAU workers have at least 1 year of experience with supporting SMI patients. Each participating centre will provide at least three experienced rehabilitation workers to the CAU condition and each worker will have an additional caseload of at most 4 to 5 research patients a year. In all three centres, a sufficient number of professionals without BPR training are available to carry out the intervention. Because of the generic nature of CAU, fidelity will not be measured in this condition. However, CAU workers will receive regular supervision according to the FACT and RIRC guidelines to ensure a high level of care.

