
### Sample size

With regard to the main outcome measure, the power analysis was based on the earlier finding that the proportion of patients engaged in meaningful activities increased by 11.5 % for BPR compared to 0 % for CAU after 1 year [9]. With this expected difference in proportion of change in both conditions, the study will have a power of 80 % (alpha = 0.05, two sided) if complete data from 2 × 90 patients is obtained. Furthermore, with regard to the economic evaluation, SF-12D is used to calculate a preference-based utility index, SF-6D. In the preceding RCT, the SF-12D [58] was not used, but scores on the WHOQOL are available [74]. For patients with rehabilitation goals in the area of societal participation, the differences between BPR and CAU after one year were 1.23 (SD 2.18). Calculating the required power of the study with this parameter, only 60 patients in each condition are needed to achieve 80 % power. Power rises to 95 % with 90 participants in each condition, which is needed for the primary outcome measure. Taking into account an average dropout rate of 20 % and a maximum dropout rate of 25 % after one year follow up, at least 225 respondents with SMI are needed for this trial. The number of patients eligible but not willing to participate will be carefully monitored to support the BIA. A pilot will be conducted for the additional 25 patients with severe and persistent eating disorders who will also participate in this study, since no information is available on the differences in change that can be expected after a year with and without BPR support for this group.

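### Patients share arm-specific rehabilitation workers, but the secondary models have no worker level, the primary model does not name its levels, and the sample size uses no design effect

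*Protocol article*

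**What the plan says.** **Delivery.** In the BPR arm (Interventions, experimental group) each centre involves at least four BPR-experienced workers, and "Each worker will have an additional caseload of four research patients a year". In the control arm (Interventions, control group), "Each participating centre will provide at least three experienced rehabilitation workers to the CAU condition". These workers have no BPR training and take at most 4 to 5 research patients a year. With three centres the stated minima are 12 BPR and 9 CAU workers. The two sets do not overlap, so workers are nested within arm and centre.

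**Secondary outcomes (Primary clinical analyses).** The levels are explicit: "each person (level 2) contributes three observations (level 1), making adjustments for participating centre, and other confounders". The treatment effect is the Time × Group interaction.

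**Primary outcome (same section).** Risk differences "will be calculated using (multilevel) regression models to be adjusted for research centre and employment in the year preceding the study". The levels are not named. Further confounders may be added if the arms differ, among them the educational level of the professional. That is a fixed covariate and not a cluster term.

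**Sample size.** Participation "increased by 11.5 % for BPR compared to 0 % for CAU after 1 year" in the preceding trial; on that basis "the study will have a power of 80 % (alpha = 0.05, two sided) if complete data from 2 × 90 patients is obtained". The only adjustment is for dropout. No ICC or design effect appears.

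**The concern.** Patients who share a worker share that worker's skill, style and local contacts, so their outcomes may be correlated. No worker treats in both arms, so randomising patients does not balance worker quality between arms, and between-worker variation goes straight into the treatment contrast. Adjusting for centre does not remove it, because several workers per arm sit within each centre.

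A model that stops at the person counts this variation as independent patient information. The standard error of the BPR effect is then too small for any positive worker ICC. A chance difference between two small groups of staff could be reported, with too much precision, as an effect of the method. This matters because the article says the interest lies in the specific techniques (Contamination between BPR and CAU) and carries the trial results into a national budget impact model (Budget impact analysis).

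**Working it through.** **1. The plan's own sample size.** Inputs: 11.5% versus 0%, two-sided alpha 0.05, 80% power.
- The pooled normal formula for two proportions gives 64 per arm, or 80 with continuity correction.
- At 90 per arm the average proportion is 0.0575. The null SE is √(0.0575 × 0.9425 × 2/90) = 0.0347 and the alternative SE is √(0.115 × 0.885/90) = 0.0336. Power = Φ((0.115 − 1.96 × 0.0347)/0.0336) ≈ 92%.
- The stated 90 for 80% power is therefore not reproduced; it is larger than the stated rates require. The total does follow: 180/0.80 = 225.

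That mismatch is a separate matter, but it bears on the power question in step 4.

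**2. Patients per worker.** The article does not give this directly, so three cases are shown.
- One year's caseload: 4 (BPR) and 4.5 (CAU, midpoint of 4 to 5).
- Two intake years less 20% dropout: 4 × 2 × 0.8 = 6.4 and 4.5 × 2 × 0.8 = 7.2. The two years are an assumption: data gathering runs three years (Time scale), less 12 months of follow-up.
- Minimum staffing with 90 completers per arm: 90/12 = 7.5 and 90/9 = 10.

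**3. Type I error of a test that ignores workers.** For each arm, DE = 1 + (m − 1) × ICC, averaged over arms. True type I error = 2(1 − Φ(1.96/√DE)). The ICC is **assumed**, at 0.01 / 0.02 / 0.05; it refers to the outcome being compared, hence to change for the Time × Group models.

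| Patients per worker (BPR, CAU) | Mean DE | True type I error of a nominal 5% test |
|---|---|---|
| 4 and 4.5 | 1.03 / 1.07 / 1.16 | 5.4 / 5.8 / 6.9% |
| 6.4 and 7.2 | 1.06 / 1.12 / 1.29 | 5.7 / 6.4 / 8.4% |
| 7.5 and 10 | 1.08 / 1.16 / 1.39 | 5.9 / 6.8 / 9.6% |

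Worked example, last row, ICC 0.05: DE = 1 + 6.5 × 0.05 = 1.325 and 1 + 9 × 0.05 = 1.45, mean 1.3875. √1.3875 = 1.178, so correct intervals are about 18% wider. 1.96/1.178 = 1.664, and the two-sided tail is 9.6%.

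A simulation with 12 and 9 workers, 90 patients per arm, a continuous outcome and 40,000 replicates gave 5.9 / 6.8 / 9.9%, and 4.9% at ICC 0.

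**4. Power if workers are accounted for, at the plan's own rates.** Divide 90 by each arm's DE. At minimum staffing and ICC 0.05 the effective sizes are 90/1.325 = 67.9 and 90/1.45 = 62.1. The formula in step 1 then gives about 80.5%. At ICC 0.01 and 0.02 it gives about 90% and 88%. These are normal approximations without a deduction for the small number of workers. Fisher's exact test at the rounded-down effective size of 64 per arm (90/1.3875) gives about 76% in the ICC 0.05 case, so that extreme case is borderline.

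**The case against.** **The primary model is not shown to omit workers.** The two-level sentence concerns secondary outcomes. The primary outcome is one binary result per patient after a year, so a multilevel model for it needs some level above the patient, and worker is not excluded. A reader might infer that the primary analysis ignores workers; the text does not establish that. This stands. What remains for the primary outcome is that the level is unnamed.

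**Random-effects detail often belongs in the SAP.** This stands in part. It covers the primary model's levels and the bootstrap, whose resampling unit is not stated under Cost-effectiveness analysis. It does not cover the secondary models, whose levels the article itself sets out without the worker.

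**The ICC is assumed and could be small.** CAU comes from multidisciplinary teams, both arms are supervised, and the intention-to-treat set keeps patients who never started. All of these could dilute worker effects. This stands: at 0.01 the error is only 5.4 to 5.9%.

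**Minimum staffing is an upper end.** Over two intake years, 12 BPR workers at four a year cover 96 patients and 9 CAU workers at 4 to 5 cover 72 to 90, against about 112 randomised per arm (225/2). The stated caseloads therefore imply more workers than the minima. This stands, and the middle row of the table is the fairer central case.

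**Power.** A reader might start from exactly 80% at 90 per arm and conclude that clustering takes the trial well below it. The article's own rates do not support that, as step 4 shows.

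**Conclusion.** The point holds for the secondary-outcome models: their written level structure leaves out the worker, and their intervals are too narrow for any positive worker ICC. For the primary outcome the fault is narrower, namely a multilevel model with unnamed levels. The sample size section has no design effect.

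The size is modest to material. Over an assumed ICC of 0.01 to 0.05, true type I error is about 5.4 to 6.9% with one year's caseload, 5.7 to 8.4% in the central case and 5.9 to 9.6% at minimum staffing. These figures rest on an ICC that the article does not give and on worker numbers stated only as minima. An error rate well above 10% would need a larger ICC together with minimum staffing, and nothing in the article supports that combination. A loss of the stated 80% power is not shown, and an effect on the bootstrap is a possibility rather than something the article states. This should be fixed before analysis; it does not invalidate the design.

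**What to change.** - Record the assigned rehabilitation worker for every patient, including those who never start.
- In the secondary models, add worker as a random effect nested within arm, or use worker-clustered standard errors with a small-sample correction (about 21 clusters at the stated minima). Keep centre as a fixed effect. Allocation follows the baseline measurement (Randomisation), so the worker effect must act on the follow-up occasions. A worker intercept that is constant over all three occasions would cancel out of the Time × Group contrast.
- In the primary model, name worker as a level.
- Resample by worker in the cost-effectiveness bootstrap, at least as a sensitivity analysis.
- State the assumed ICC and the resulting design effect beside the power statement.

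The cost is one identifier per patient and a few lines of analysis text. No extra patients and no change to treatment are needed. The price is somewhat wider confidence intervals: about 2 to 8% wider with one year's caseload and 4 to 18% at minimum staffing over ICC 0.01 to 0.05 (the square root of the mean design effect).
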